**Figure 2. f2:**
[figure not shown]
Planned sample collection time points and subsequent sample processing sequence.

**
*Resistance markers study.*
** We will monitor changes of SP, AQ, resistance in the three intervention districts, receiving SMC using only SPAQ (Nabilatuk, Kotido and Moroto) plus the two research districts where the SMC will be implemented using both SPAQ and DP (Amudat and Nakapiripirit), while the DP resistance will be monitored only in the later. A baseline cross-sectional survey will be conducted based at the health facilities before SMC project implementation as well as an endline survey following one complete round of SMC distribution to measure the prevalence of molecular markers associated with resistance to SP/DP in symptomatic children under five years of age with a positive RDT attending selected health facilities in the intervention and control areas.

The key markers of resistance to be monitored are: dihydrofolate reductase (dhfr): codons 108, 51, 59 and 164; dihydropteorate synthetase (dhps): codons 431, 437, 540, 581 and 613; Pf chloroquine resistance transporter gene (pfcrt): codons 72-76; Pf multidrug resistance gene 1 (pfmdr1): codons 86, 184 and 1246, Plasmepsin 2 (plm2) and K13 mutations of significance

**
*Process evaluation component.*
** Once interview participants are identified for potential recruitment, they will be approached by a research assistant who will share more information about the study and invite their participation. If willing, a meeting will then be set up at a time and location that is convenient for the individual, where further information will be shared about the study including a written information sheet provided to all participants.

In-depth interviews and focus group discussions based on topic guides will be utilized to explore insights on SMC including acceptability and thoughts regarding the experience of implementation.

### Data analysis

**
*cRCT component.*
** We will accomplish data analysis using Stata and excel. The proportion command, with 95% confidence intervals calculated using a logit transform will be used to compute coverage. Population size weights will be applied with the svy: command as appropriate for the estimates of coverage indicators whereby a self-weighting sample was not possible to achieve. The pertinent indicators will be calculated using proportions per district and an average across both districts. The confidence interval (CI) of 95% will be used to provide a range of values around the estimate within which selected result will be expected to fall.

Data from HMIS will be retrospectively analysed to identify epidemiological trends in malaria in the study districts by age group. Summary statistics will be computed and data will be graphically presented by month over the study period.

**
*Chemoprevention efficacy cohort study.*
** Relevant mutations distributions and proportions will be analysed comparing parasitological efficacy between groups of mutations. Analysis of the blood drug concentrations will be done as a cohort by mean, median and standard deviation, and statistical tests of their associations with treatment outcomes, precisely drug levels on day seven. Outliers with low levels of drug concentration based on the outcome measures described will be focused upon. Positivity on day 28 will be associated with the antimalarial drug resistance genotype. Chemoprevention failure rates will be reported on as the cumulative failure rate using Kaplan-Meier analysis of the proportion. Time to event analysis will be incorporated to assess duration of SMC protection.

**
*Resistance markers study.*
** The prevalence of Pfdhps, Pfdhfr Pfcrt and Pfmdr1 and K13 alleles will be measured in parasites obtained from smear positive children. Additionally, the copy number of Pfplm2 will also be assessed.

**
*Process evaluation component.*
** The data will be analysed thematically. Both key informant interviews and FGDs will be audio-recorded and thereafter transcribed verbatim i.e. in the real words (or equivalent translations) used by the informants. These will be organised according to findings relating to SMC acceptability, implementation, and views and experiences with SMC more broadly. Initially, open, descriptive coding will be used in order to ensure interpretations are grounded in participants’ accounts as much as possible, and that findings are generated inductively, as well as exploring pre-determined areas of investigation (for example, relating to acceptability of SMC). The transcribed data will be entered into Nvivo 12 for analysis and coded based on both pre-determined themes as well as those that emerged from the data. Codes and themes will continuously be refined as the analysis progresses. The coded text under each code / theme will provide the basis for determining the patterns and meanings in the data, comparing across data from different respondent groups, and for making arguments and conclusions. Relevant quotations will also be identified and included in the analysis report.

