## Protocol

### Aims and objectives

This study phase aims to test the feasibility, effectiveness, and chemoprevention efficacy of SMC with SPAQ and DP in Karamoja region in Uganda, where malaria transmission is highly seasonal, and inform malaria policy in Uganda. Specific objectives include: 1) to determine the effectiveness of SMC with SPAQ and DP in terms of its reduction in incidence of malaria infection among children aged 3–59 month for SPAQ and children 6–59 months for DP; 2a) to conduct a prospective chemoprevention efficacy cohort study to determine if SPAQ and DP clear existing parasitemia and provide 28 days of protection from infection and whether drug concentrations and/or SPAQ or DP drug resistance influence the protection duration of these two SMC regimen; 2b) to assess the safety of DP in children 3–6 months through pharmacometric analysis; 3) to conduct a resistance markers study in children 3–59 months in the two research districts plus the three standard intervention districts to measure changes in resistance marker prevalence over time; and 4) to assess the impact of the SMC implementation model, determining process, costing and acceptability outcomes for the intervention.

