** Children will be screened at the community level by research assistants with the help of VHTs and referred to a designated study clinic for further assessment and non-randomized recruitment. At the study clinic, study clinicians will confirm eligibility criteria through conversation with the caretaker and obtain informed consent. Enrolled children will receive SMC via directly observed therapy (DOT) over the first three days and will have malaria thick smears and dry blood spots (DBS) taken at day 0, 2, 7, 14, 21 and 28 throughout and after administering a single cycle of SPAQ or DP. In addition, the study clinician will assess if the child received other treatment or experienced any problem during all the scheduled sample collection days (Day 0, 7, 14, 21, 28) as well as bed net usage. Caregivers and guardians will also be reminded at each visit to seek care at a health facility or from a community health worker if the child becomes febrile. Children who become febrile and are confirmed on HPR2-pLDH RDT between day 0 and day 28 will have an additional DBS taken and then treated using standard guidelines. All DBS samples will be processed for all of the SMC drugs on days 7 and for sulfadoxine, amodiaquine and piperaquine for day 28. Individual surveys on day 28 after the final DBS is taken will be conducted to determine if the child received other treatment or experienced illness over the past month of study implementation. On day 0 and day 28, they will also be processed to ascertain low density parasitaemia estimates through quantitative polymerase chain reaction (qPCR).
Figure 2 below depicts the planned sample collection time points and subsequent sample processing sequence). We aim to recruit participants from Nakapiripit, one of the two research districts.

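### The cohort's resistance-genotype association uses positivity on day 28, which is likely to miss febrile breakthroughs treated before that day

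*Protocol article*

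**What the plan says.** All references are to the protocol article and its chemoprevention efficacy cohort.

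- **Aims and objectives, objective 2a.** Besides clearance and 28 days of protection, the cohort is to determine "whether drug concentrations and/or SPAQ or DP drug resistance influence the protection duration of these two SMC regimen".
- **Recruitment and data collection.** Children have "malaria thick smears and dry blood spots (DBS) taken at day 0, 2, 7, 14, 21 and 28". Between visits, "Children who become febrile and are confirmed on HPR2-pLDH RDT between day 0 and day 28 will have an additional DBS taken and then treated" under standard guidelines.
- **Data analysis.** Four sentences bear on the point:
  - on genotype and outcome: "Positivity on day 28 will be associated with the antimalarial drug resistance genotype";
  - on mutation groups: "Relevant mutations distributions and proportions will be analysed comparing parasitological efficacy between groups of mutations";
  - on failure: "Chemoprevention failure rates will be reported on as the cumulative failure rate using Kaplan-Meier analysis of the proportion";
  - on duration: "Time to event analysis will be incorporated to assess duration of SMC protection".

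Only the first of these links genotype to an outcome at a stated time, and that time is day 28.

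**The concern.** Antimalarial treatment is meant to clear parasites. A child who breaks through early, is treated and returns on day 28 will probably be negative then. This is not certain: a child treated shortly before day 28 may still be positive by qPCR. Without a rule that carries the earlier event forward, the child enters the genotype association as a non-failure or drops out of it.

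These failures matter for objective 2a, because an early febrile breakthrough is direct evidence that protection was short. A single reading on day 28 does not distinguish a child protected throughout from one who failed early and was treated. Such events are also expected: the Study setting section explains that the cohort district was chosen partly because higher malaria rates should reveal more breakthroughs.

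**Working it through.** **Step 1: follow one child through the text.** Take a child with an RDT-confirmed fever well before day 28.

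1. Recruitment and data collection: the extra blood spot is taken and the child is treated.
2. Day-28 sample: probably negative, for the reason given above.
3. Genotype association on day-28 positivity: the child is a non-failure, or absent if treated children are excluded. If instead only parasites found on day 28 are genotyped, the child contributes nothing. The breakthrough is missed under each of these readings.
4. Other sentences: the comparison across mutation groups names no time point, and the time-to-event sentence does not mention genotype. Neither states that the breakthrough is counted against genotype.

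**Step 2: what the article gives for the size.** Table 1 gives a cohort of 1,250. The article gives no failure rate, no share of failures treated before day 28 and no number of children with a genotype. The size cannot be derived from it.

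**Step 3: optional illustration of direction.** Every rate here is an assumption. Let p be the true risk of failure by day 28 and t the share of failures treated before day 28. Assume that all treated children are negative on day 28, that all untreated failures are positive then, and that every child can be placed in a genotype group. Then:

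- treated children counted as negative: observed risk = p(1 − t);
- treated children excluded: observed risk = p(1 − t)/(1 − pt).

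With p = 0.20 (resistant) and p = 0.10 (sensitive), the true ratio is 2.00 and the true difference is 10 points.

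| t resistant | t sensitive | Ratio, counted negative | Ratio, excluded |
|---|---|---|---|
| 0.25 | 0.25 | 0.150/0.075 = 2.00 | 0.1579/0.0769 = 2.05 |
| 0.50 | 0.25 | 0.100/0.075 = 1.33 | 0.1111/0.0769 = 1.44 |
| 0.25 | 0.50 | 0.150/0.050 = 3.00 | 0.1579/0.0526 = 3.00 |

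With equal shares the ratio barely changes. The difference, with treated children counted as negative, falls from 10 to 7.5 points (0.150 − 0.075), so information is still lost. With unequal shares the ratio moves down or up according to which group is treated early more often.

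**The case against.** The strongest defence is that the article condenses a fuller protocol. Its Data analysis section refers to outcome measures that it does not itself set out, and the figure showing how samples are processed is not available here. The comparison across mutation groups is not confined to day 28, and nothing bars genotype from the time-to-event analysis. Study clinicians ask about other treatment at scheduled visits, so treated children can be identified. Much of this stands: the fuller documents may already count these children correctly in another analysis. It does not remove the point, because day-28 positivity is a stated choice of outcome for this association, and that choice fits objective 2a badly.

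A reader might infer more than the text supports:

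- **That the plan contradicts itself**, scoring the same child as a failure in the Kaplan-Meier rate and a non-failure in the association. The article never defines Kaplan-Meier failure. Counting a febrile breakthrough there is natural, but it is an inference.
- **That the association is diluted.** No direction can be claimed. Equal treated shares leave a ratio almost unchanged, and the article gives no information on whether the shares differ.
- **That a number of lost failures can be stated.** Any such figure rests on assumed rates, and the number of children with a usable genotype is not given.
- **That genotype must come from day-0 parasites.** This would measure exposure alike in failures and non-failures. However, it drops children uninfected at baseline, who inform protection against new infection, and a later failure may be a new infection with a different genotype. It is a trade-off, not a correction.

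**Conclusion.** The point holds as a poorly fitting outcome choice in one cohort analysis. Used as written, day-28 positivity is likely to leave out febrile breakthroughs treated earlier, and these bear directly on whether resistance shortens protection. The conclusion rests on two stated facts, the day-28 outcome and treatment before day 28, and on one assumption: that treatment usually clears parasites by day 28. Bias on a ratio scale also requires early treated failure to differ by genotype. Its direction and size are unknown.

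The point does not show that the Kaplan-Meier failure rate is wrong, and it does not touch the cluster-randomised trial or its primary endpoint. It is worth considering, with medium confidence.

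**What to change.** In the genotype association:

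1. Replace day-28 positivity with chemoprevention failure by day 28, preferably analysed as time to failure. Failure is the first of an RDT-confirmed febrile breakthrough, a recurrent positive scheduled smear after initial clearance, or positivity on day 28.
2. Use the same definition in the Kaplan-Meier analysis, and write it down once for both.
3. Include the fever-time blood spots among the samples genotyped.
4. Report how many children were treated before day 28 and how many failures have no genotype.
5. Keep day-28 positivity as a secondary outcome.

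The Study status section reports that data collection is complete and that cleaning and preliminary analysis are in progress. The change is therefore analytic and uses samples the protocol already plans to take. It costs slightly more analysis and possibly a few more samples to genotype. Some failures will still lack a genotype, which is why item 4 asks for the count.

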### Data management

For the cRCT component (1), using computer aided personal interview (CAPI), which allows for in-field data entry and server synchronisation, data collected will be verified for quality assurance purposes by the quality assurance officer in field and uploaded daily to the SurveyCTO platform. The uploaded files will undergo additional consistency checks, cleaned and saved into Stata. Extensive data cleaning will be done at the end of the fieldwork.

For the chemoprevention efficacy and safety studies, all clinical data will be recorded onto standardized case record forms (CRFs) by IDRC study clinicians. Data will then be entered directly from CRFs into a computerized database or transferred from the CRFs onto standardized data extraction forms and then into a computerized database. All computerized data will be double entered to verify accuracy of entry.

For the resistance markers study, data will initially be managed at health facilities-level by field workers with support from the IDRC Data Management Team (DMT). They will send the pVHTr questionnaires to the IDRC once sample collection has been completed. Data will then be entered by a data entry clerk using specific software for clinical data management. Rigorous consistency checks will be created to reduce errors during data entry.

For the process evaluation, data will be stored without any participant-identifying information (with use of pseudonyms and removal of job title or other identifying information), in a password-protected format. Raw data collected and analysed will not be shared with anyone other than the researchers of this study.

### Eligibility criteria

Inclusion and exclusion criteria for each objective are detailed in
Table 2 below.

**Table 2. T2:** Eligibility Criteria.

Inclusion criterion	(1)	(2)	(3)	(4)
Children between 3–59 months	x	x	x	
Being resident in the study area	x	x	x	
Afebrile with no other malaria associated symptoms in the past 48 hours or at time of recruitment	X	X		
Consent to participate in the study obtained	X	X	X	
Willingness and ability of the child’s guardians to comply with the study protocol for the duration of the study including attending a designated health centre if their child has malaria symptoms during the data collection period	x	X		
Can comply with 3 days DOT of standard SPAQ or DP regimen (day 0–2		x		
Clinical signs and symptoms suggestive of malaria infection: fever (axillary temperature ≥37.5ºC) or history of fever in the preceding 24 hours.			X	
Positive RDT			x	
A person aged 18 years or older with primary or caring responsibility for the feeding and daily care of at least one child aged 3–59 months, who has been resident in Nabilatuk, Kotido, Moroto, Amudat or Nakapiripirit prior to the beginning of the SMC pilot				x
Community members, community leaders, religious leaders				X
Village Health Teams (VHTs) involved in the distribution of SMC in Nabitatuk, Kotido, Moroto, Amudat and Nakapiripirit				X
Community Health Workers, Community Distributors				X
District level health officials (District Health Officers, Malaria Focal Persons)				X
Provincial level health officials				X
Implementing partners				X
National level policy makers				X
Gender experts and/or gender advocates				x
Exclusion criterion	(1)	(2)	(3)	(4)
Malaria symptoms (tympanic fever ≥ 37.5°C or history of fever in past 48 hours)	X	X		
Known allergy to medicine provided	X	X		
Receiving a sulfa-based medication for treatment or prophylaxis, including co-trimoxazole (trimethoprim– sulfamethoxazole)	X	X		
Individuals receiving azithromycin due to the antimalarial activity of azithromycin	X	x		
Severe malnutrition according to WHO guidelines	X	X		
Recruited in any other SMC study element	X	X		
Children with HIV or ARV use	X	X		
Children with a history of severe adverse reaction to SP, AQ or DP or have used SP within the previous month before recruitment	x	X		
Treatment of uncomplicated malaria with DP in the past 28 days		X		
Chronic illness of any kind		X		
Recruited in cRCT or any other studies		X		
Treatment with an ACT in previous 2 weeks		X		
Any signs or symptoms of severe malaria			X	
Negative RDT			x	
Any individual who refuses consent to participate	x	x	x	X
Individuals aged under 18 years				x

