### Study setting

The study will be conducted in five districts of Karamoja region as shown in
Figure 1 below. The cRCT will be conducted in Amudat. The chemoprevention component will be conducted in Nakapiripirit because SMC has not been previously implemented in this location therefore drug resistance selection pressure from a previous year of SMC implementation will be avoided or minimized and malaria rates are expected to be higher allowing for a greater detection of breakthrough infections. The resistance markers component will be conducted in all five districts inclusive of Nabilatuk, Kotido and Moroto, as well as the process evaluation for assessment of the SMC implementation model.

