### Population

Eligible participants for receiving SMC will be male or female children with no fever, aged 3–59 months for any of the SMC cycles, staying in the districts of Kotido, Moroto and Nabilatuk districts (where delivery is continuing from Phase 1 and where coverage surveys will be conducted in Phase 2), and randomly-selected areas in Amudat and Nakapiripirit.

Additionally, other key stakeholders who will be sampled include health workers participating in implementing SMC, health officials at different levels of the health system, community leaders, and caregivers of children below ten years of age, (see
Table 1 for estimated population sizes).

**Table 1. T1:** Sample sizes for each objective.

Objective	Study population	Estimated sample size
1	cRCT: Sample of eligible children in Amudat district of age 3–59 months, resident in the study area for at least a month, planned for DP and SPAQ	4,270
2a	Chemoprevention efficacy cohort study – children under 3–59 months for SPAQ and 6-59 months for DP	1,250
2b	Safety of DP in 3–6 month old children through pharmacometrics to low dose DP.	30
3	Resistance Marker study – children under 5	1,500
4	Assessment of the SMC implementation model, deciding the process, costing and acceptability outcomes of the intervention	144
**Total number of participants:**		**7,194**

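### The cohort's entry criteria bar any recent SP but bar recent DP only when given as treatment, so a child who has just had DP as SMC can enter

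*Protocol article*

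**What the plan says.** All references are to the protocol article.

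- **Eligibility criteria, Table 2, cohort column.** Prior SP excludes a child whatever it was given for: the row covers those who "have used SP within the previous month before recruitment". Prior DP appears only as "Treatment of uncomplicated malaria with DP in the past 28 days". A third row excludes "Treatment with an ACT in previous 2 weeks". A fourth excludes "Recruited in cRCT or any other studies".
- **Recruitment and data collection, resistance markers study.** SMC with both regimens is delivered in the cohort's own district: "the two research districts where the SMC will be implemented using both SPAQ and DP (Amudat and Nakapiripirit").
- **Population.** Delivery there is limited to part of the district: "and randomly-selected areas in Amudat and Nakapiripirit".
- **Study design.** The programme runs five cycles, one a month, from June to October 2022.
- **Recruitment and data collection, cohort study.** Samples are taken up to day 28, "throughout and after administering a single cycle of SPAQ or DP". Recruitment is not randomised. Clinicians ask about other treatment on the scheduled days, including day 0.
- **Study setting.** Nakapiripirit was chosen "because SMC has not been previously implemented in this location"; the reason given is selection pressure from an earlier year of SMC.

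**The concern.** The cohort is meant to show what one observed course does: whether it clears existing parasitaemia, how long it protects up to day 28, and how drug levels relate to outcome. Drug left over from an earlier course blurs all three. It can reduce the infections present on day 0, add to the concentrations measured on days 7 and 28, and delay infections that would otherwise have appeared.

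The article itself treats this as relevant for DP. It sets a 28-day look-back when DP was given as treatment, cites the drug's long half-life as the reason to consider it for SMC (Introduction), and assays piperaquine on day 28. Yet the look-back does not name DP given as SMC, although the programme gives it in the same district in the same season. The SP row has no such restriction. The two regimens therefore face different entry filters for the same kind of prior exposure.

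**Working it through.** **What can be checked.** Table 1 adds up: 4,270 + 1,250 + 30 + 1,500 + 144 = 7,194, as stated. The cohort's 1,250 comes with no inputs, and no stated figure bears on prior exposure. What follows is calendar arithmetic on the Table 2 rows.

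**Inputs.** If cycles fall on the same date each month from June to October, the gaps are 30, 31, 31 and 30 days. A strict 28-day gap is added as a lower bound. The look-back windows are those in Table 2: a month for SP (taken as 28 to 30 days), 28 days for DP as treatment and 14 days for ACT as treatment.

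**Assumptions.** Each programme course is dated to one day. The child took the last programme cycle u days before day 0, with u = 1, …, G, where G is the gap. Each u counts equally.

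**Formula.** A row with window W that applies to the exposure excludes u ≤ W. The share of enrolment days on which the child remains eligible is (G − W)/G, or 0 if W ≥ G. A row that does not apply has W = 0.

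| Exposure in the last cycle, and reading of Table 2 | W | G = 28 | G = 30 | G = 31 |
|---|---|---|---|---|
| DP as SMC, literal text | 0 | 28/28 = 100% | 30/30 = 100% | 31/31 = 100% |
| DP as SMC, ACT row read to include SMC | 14 | 14/28 = 50% | 16/30 = 53% | 17/31 = 55% |
| SPAQ as SMC, month = 28 days | 28 | 0% | 2/30 = 7% | 3/31 = 10% |
| SPAQ as SMC, month = 30 days | 30 | 0% | 0% | 1/31 = 3% |
| DP as SMC, if the DP row covered any use | 28 | 0% | 2/30 = 7% | 3/31 = 10% |

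The last row shows that widening the DP row to any use would bring it to the 0–10% that the SP row already achieves.

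**Do other rows close the gap?** The study-participation rows name recruits to the cRCT, other studies or other SMC study elements. They do not name a child who simply receives programme SMC. Such children exist: the Introduction plans DP for about 15,000 children, while the cRCT, cohort and pharmacokinetic sub-study together number 4,270 + 1,250 + 30 = 5,550. Even if every one of those took DP, 15,000 − 5,550 = 9,450 recipients would lie outside them. How many live in Nakapiripirit is not given.

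**The case against.** The strongest reply is that the gap may be small in practice. DP as SMC reaches about 15,000 of 270,000 children (5.6%), and delivery in Nakapiripirit covers selected areas only. Children enrolled at the first cycle, or from areas without delivery, carry nothing over, since the district had no SMC before. DP is an ACT, so a site might apply the two-week row to SMC as well. All of this stands as a limit on size. It does not remove the gap: the ACT row is worded as treatment, and even the generous reading leaves about half the enrolment days open.

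A reader might infer more than the article supports:

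- **That children are re-dosed by the programme before day 28.** Cycles 30 or 31 days apart exceed the 28-day follow-up. Overlap requires enrolment away from the cycle date, a home in a covered area and no skipping by the distributors. The article states none of these, and the full protocol may settle them. The SP row also prevents recent SPAQ recipients from being enrolled evenly through a cycle.
- **That the analysis ignores other treatment.** Visits record it, and censoring rules commonly sit in the full protocol or SAP.
- **That the site rationale requires children with no SMC at all in 2022.** It concerns a previous year only.

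**Conclusion.** The point holds as a wording fault with a real route to bias. Followed literally, Table 2 admits a child given DP as SMC in the preceding cycle on 100% of enrolment days (50–55% if the ACT row is stretched to cover SMC), against 0–10% for a child given SPAQ as SMC. These shares rest on cycles 28 to 31 days apart and equal weight for each enrolment day. They describe eligibility, not the number of children actually enrolled.

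Neither the size nor the direction of any bias between regimens can be computed. It is tempting to conclude that the rule tilts the results towards DP. The article does not say which regimen a former DP-SMC child would receive in the cohort: carry-over would flatter DP if the child were given DP, and SPAQ if given SPAQ. Since recruitment is not randomised, prior exposure cannot be assumed to balance between the groups.

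**What to change.** 1. Reconcile the SP and DP rows of Table 2 with the statement that both regimens are delivered as SMC in Nakapiripirit, so that the DP look-back covers DP for any purpose, including SMC, as the SP row does for SP.
2. Study status says that data collection has ended, so new wording alone changes nothing. Flag cohort children with DP as SMC in the 28 days before day 0, using programme or distribution records where available and the day-0 question on other treatment. Report parasitological efficacy, drug-level associations and Kaplan-Meier failure with and without the flagged children. If the records cannot show prior exposure, say so as a limitation.
3. Confirm in the full protocol or SAP how non-study SMC before day 28 is handled. Blanket censoring at any antimalarial is not advised, because it could censor children treated for a malaria episode that is itself a failure.

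The cost is some record linkage and a slightly smaller set in the restricted analysis. SMC record cards are described only for the cRCT, so linkage for the cohort may be incomplete. If few children are flagged, the main results lose almost nothing and are easier to defend.
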